#### Eligibility criteria

All women giving birth in the 21 municipalities during the project period from April 2022 to end of 2023 are eligible for inclusion in the trial provided they are: 1) ≥ 15 years old, 2) intend to breastfeed their infant, 3) were discharged from the hospital less than seven days after giving birth^1^, 4) gave birth to a singleton, and 5) had a term born child. The exclusion criteria are: 1) insufficient Danish and English language skills to respond to questionnaires and understand the support conveyed in either Danish or English, 2) known substance use disorder or use of illegal drugs, and/or 3) known morbidity or disablement affecting their ability to breastfeed. Fathers/partners are invited to participate based on their partner’s eligibility and must be able to understand Danish or English.

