### Sample size and power calculations

For sample size calculation, an estimated eight clusters in each arm were used, totalling 16 clusters. Expected participation rate was 80% with 30% attrition from the first questionnaire at one week postpartum to the third questionnaire at four months postpartum. A power calculation was made using breastfeeding frequencies from 2016 made available from The National Child Health Register [50]. The ambition was to raise the proportion of women breastfeeding at four months in the intervention clusters to the national level. In the design phase, we obtained data on the mean prevalence of breastfeeding at four months in the project regions (49%) and at national levels (56%) in 2016 from the National Child Health Register. The observed difference in the proportion of women exclusively breastfeeding for a minimum of four months corresponds to an odds ratio of 1.32. In the power calculations, an interclass correlation coefficient (ICC) of 0.001, as observed in the previous intervention study [27], was used. Reaching a statistical power of 80% with a 5% significance level is thus achievable provided data are collected from 111 mothers in each cluster. In each cluster, the sample size was extended to ensure that a minimum of 52 mothers were young or had low educational attainment. This yields a power of 80% to investigate an increase in exclusive breastfeeding at four months from 45 to 55% in this subgroup.

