### Statistical methods

We use random allocation to remove any influence of both measured and unmeasured variables on treatment allocation. Before conducting regression analyses, descriptive statistics will be applied to assess selection into the trial, baseline equivalence of trial arms and loss to follow-up.

Regression analyses will be applied when analysing primary outcomes. We will account for the clustered nature of data by using random effects models for binary and continuous outcomes [51] and shared frailty models for analysing time-to-event and recurrent events in continuous outcomes [52]. Intention-to-treat analyses will be conducted. These analyses will include all mother-infant dyads in the relevant trial arms irrespective of their compliance or loss to follow-up. Complete-case analyses will be conducted restricted to observations with available outcome measures [53]. For the intention-to-treat analyses, the survey data will be linked to the Danish national registers including all births; and missing outcome data will be handled by inverse probability weighting and missing covariates by multiple imputation from the registers. The probability weights will be estimated by conducting logistic regressions with outcome data (yes vs. no) as dependent variable and the following baseline variables as predictors: maternal educational, maternal age, cohabitation status, partner’s education, household income, occupational status, maternal smoking status, maternal BMI, and maternal as well as paternal psychiatric histories.

The effect of the intensified intervention will be examined by including an interaction term between treatment arms and a binary indicator of the mother being young or having low educational attainment.

All models will be analysed with treatment alone and adjusted for known predictors for breastfeeding duration collected in the survey (smoking status, maternal age, maternal education, parity, mode of delivery, maternal BMI and cohabitation status) and for design variables used in the randomisation (region of Denmark and number of annual births (< 900 births/year vs. ≥ 900 births/year). As the randomisation will hopefully have distributed the characteristics evenly between trial arms, these adjustments are made to increase the robustness of the effect estimations. Missing predictors will be imputed using multiple imputations and the results compared to the complete case analysis.

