To validate the robustness of the results, the following sensitivity analyses will be performed: First, data will be restricted to mothers having received the full intervention, i.e., including pregnancy visits (June 17 and onwards), to assess the effect of receiving the full intervention compared to mothers having received the intervention without the pregnancy visits (April 26 to June 16); second, observations with no records in registries, most likely an indicator of recent immigration, will be excluded to test whether the effect of the intervention is higher among individuals familiar with the Danish healthcare system than among those who are not familiar with the system; and, third, the worst case scenario assigning no breastfeeding at four months postpartum to all individuals with missing registrations will be used to gauge the minimum effect of the treatment.

The Danish nationwide registries will further allow detailed assessment of selection into the trial (Table 3). Selection into the trial will be examined using register data from 2022, again using inverse probability weighting to assess potential selection effects.

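### The register-record sensitivity analysis is meant to compare effects between two groups, but the plan only removes one of them and describes no estimate or test of the difference

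*Protocol article*

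**What the plan says.** The Statistical methods section of the Protocol article introduces three further analyses with "To validate the robustness of the results, the following sensitivity analyses will be performed". The second concerns "observations with no records in registries, most likely an indicator of recent immigration". These mothers "will be excluded to test whether the effect of the intervention is higher among individuals familiar with the Danish healthcare system", and the comparator is then named: "than among those who are not familiar with the system".

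Earlier in the same section, a question of the same kind is handled differently. The effect of the intensified intervention is to be examined by "including an interaction term between treatment arms and a binary indicator of the mother being young or having low educational attainment". The difference-in-difference section says its analyses will use an interaction term in the same way.

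**The concern.** The aim and the operation do not match. The aim asks whether the intervention effect is larger in one group of mothers than in another. The operation removes the second group, so the restricted analysis holds no information on it.

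An analyst following the text has two choices. One is to report the restricted estimate alone, which describes mothers with records and says nothing about the comparison. The other is to set it beside the full-sample estimate and judge the change informally. The two samples overlap, and the change is a diluted form of the contrast of interest. A small change could then be taken to mean that the effect is the same in both groups, when it would also be expected if the excluded mothers gained nothing.

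What is at stake is the interpretation of one secondary analysis: a statement about effect modification by record status that no estimate or test supports.

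**Working it through.** **Planning figures.** The point contests no number in the plan, but the illustration borrows its rates, so they were checked first. Inputs from Sample size and power calculations: 49% and 56%, intraclass correlation 0.001, 80% power, 5% significance (taken as two-sided), and "an estimated eight clusters in each arm were used, totalling 16 clusters".

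- Odds ratio: (0.56/0.44) / (0.49/0.51) = 1.32, as stated.
- Independent sample per arm, standard two-proportion formula without continuity correction: [1.96 × √(2 × 0.525 × 0.475) + 0.842 × √(0.49 × 0.51 + 0.56 × 0.44)]² / 0.07² = 798.
- Design effect at 111 per cluster: 1 + 110 × 0.001 = 1.11. Then 798 × 1.11 / 8 = 110.7, so 111 per cluster, as stated.

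**What exclusion estimates.** Let f be the share of mothers without records (assumed equal in both arms), d_R the effect in those with records and d_N the effect in those without. On the risk-difference scale:

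- full-sample effect ≈ (1 − f) × d_R + f × d_N
- restricted effect = d_R
- restricted minus full ≈ f × (d_R − d_N)

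The aim concerns d_R − d_N. Exclusion gives d_R only. Setting it beside the full estimate gives the contrast multiplied by f.

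**Size of the shift.** The plan does not give f, so 2%, 5% and 10% are assumptions. Take d_R = 7 points (the planning difference, 56% − 49%) and d_N = 0:

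| f | Shift on exclusion = f × 7 |
|---|---|
| 2% | 0.14 points |
| 5% | 0.35 points |
| 10% | 0.70 points |

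**Precision of a direct contrast.** Table 2 of the article gives 11 intervention municipalities out of 21, leaving 10 controls. With 111 mothers in each, the arms have 1,221 and 1,110 mothers. Using a per-person variance of 0.25 and ignoring clustering:

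- 0.25 × (1/1221 + 1/1110) = 0.000430
- SE of (d_R − d_N) = √[0.000430 / (f × (1 − f))]

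| f | SE of contrast | 95% half-width (1.96 × SE) | SE of shift = f × SE | z, either way |
|---|---|---|---|---|
| 2% | 14.8 points | 29 points | 0.30 points | 7/14.8 = 0.5 |
| 5% | 9.5 points | 19 points | 0.48 points | 7/9.5 = 0.7 |
| 10% | 6.9 points | 14 points | 0.69 points | 7/6.9 = 1.0 |

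The last two columns show that the shift, judged against its own standard error, carries the same evidence as the interaction. With the planning figure of 8 clusters per arm (888 mothers), the contrast standard errors are 17.0, 10.9 and 7.9 points, and the power to detect a 7-point contrast is about 6%, 9% and 14%.

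**The case against.** Four objections deserve an answer.

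**Nested estimates can in principle carry a test.** A reader might infer that exclusion can never test an effect difference. That goes too far. The shift is zero exactly when the two effects are equal, and a test allowing for the overlap gives the same z as the interaction. For the same reason, the shift should not be judged against the standard error of the overall effect, which is the wrong yardstick. This objection stands. It does not rescue the text, because no such test is described, and comparing by eye is not one.

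**The group's size is unknown.** A reader might also infer that the group is too small to matter, perhaps from the eligibility criterion on "insufficient Danish and English language skills to respond to questionnaires". The article gives no count or share of mothers without records, and the language criterion does not supply one. Every figure that depends on f is conditional.

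**It is only a robustness check, and detail may sit in an analysis plan.** Exclusion is a legitimate robustness check, and an article may leave out how results will be set side by side. But this article states both the operation and its purpose, and the purpose goes beyond robustness. That mismatch is in the text itself.

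**The equity question is handled elsewhere.** A reader might infer that the trial's conclusion on social inequality is at risk. It is not. That question is defined by young maternal age or low education, and an interaction term is already planned for it. Nor does the article state any rule for reporting the register-record result, so a misleading statement is a possibility, not a planned output.

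**Conclusion.** The point holds as a mismatch between stated purpose and stated method in one secondary analysis. The plan promises a comparison of effects by familiarity with the health system and describes only a restriction to one side of it. Its importance is minor.

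The illustrative size is a shift of 0.14 to 0.70 points for a 7-point contrast. It rests on an assumed share of 2% to 10%, equal in both arms, and on the risk-difference scale; on the odds-ratio scale the relation is only approximate. A larger share would give a larger shift and a more precise contrast. The logical gap does not depend on these assumptions, since no value of f makes a restricted estimate describe the mothers it leaves out.

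An interaction would not add much power. Its gain is that the contrast and its uncertainty are shown openly, so that lack of information is not mistaken for equal effects.

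**What to change.** Address the question with all mothers in the model and an arm-by-register-record interaction, as the plan already does for young or low-education mothers. Report the effect and confidence interval in each group and for the contrast, give the number of mothers without records in each arm, and state that precision will be low if that group is small.

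Keep the exclusion if wanted, but describe it only as a check that the main result does not depend on these mothers, and delete the claim that it tests an effect difference.

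The cost is one model term and one reworded clause. No further data are needed, and the drawback is an interval that may be too wide to support any conclusion. If the investigators do not want the interaction, deleting the claim alone removes the mismatch, at the price of leaving the question unanswered.

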#### Primary outcome measure

Proportion of mothers who exclusively breastfeed at four months postpartum.

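### The third sensitivity analysis codes every missing outcome in both arms as not breastfeeding and calls this the worst case and minimum effect, but it is not a lower bound

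*Protocol article*

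**What the plan says.** The primary survey outcome is binary: "Proportion of mothers who exclusively breastfeed at four months postpartum" (Protocol article, Primary outcome measure). For the intention-to-treat analyses, Statistical methods handles missing outcomes by inverse probability weighting on listed baseline variables, with complete-case analyses alongside. Three sensitivity analyses follow. The third is introduced as the worst case: "assigning no breastfeeding at four months postpartum to all individuals with missing registrations will be used to gauge the minimum effect of the treatment". It makes no distinction by arm. Sample size and power calculations expects "30% attrition from the first questionnaire at one week postpartum to the third questionnaire at four months postpartum" and gives no figure by arm. The planning rates are the "mean prevalence of breastfeeding at four months in the project regions (49%) and at national levels (56%) in 2016".

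**The concern.** A worst case for a treatment comparison has to be unfavourable to the treatment. That means failure for missing intervention mothers and success for missing controls. Giving both arms the same value lowers both proportions. What happens to their difference depends on how much is missing in each arm and says nothing about the floor.

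This matters because the other two sensitivity analyses restrict the population (to mothers offered the pregnancy visit, and to mothers with register records). Only the third changes the assumption about missing outcomes, so it is the one check on the assumption behind the weighting. If its result is read as a minimum, readers will credit the trial with a floor that its data do not provide.

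Equal and similarly informative missingness cannot be taken for granted. The Discussion says that allocation cannot be concealed. In the intervention arm only, young or low-education mothers are offered extra telephone calls, and these stop when breastfeeding stops (Intensified intervention).

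**Working it through.** **Inputs.** From Sample size and power calculations: 49% and 56%; 30% attrition; "an estimated eight clusters in each arm were used, totalling 16 clusters"; ICC 0.001; 111 mothers per cluster. Assumed here: the 30% is the missing share for this scenario, 56% v 49% holds among responders, and the arm-specific splits below are illustrative.

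**The plan's own figures reproduce.** The odds ratio is (0.56/0.44)/(0.49/0.51) = 1.325, against the stated 1.32. Two proportions at two-sided 5% (sidedness assumed) and 80% power need 798 per arm. The design effect is 1 + (111 - 1) × 0.001 = 1.11. Then 798 × 1.11 = 885.8 per arm, and 885.8/8 = 110.7, which rounds up to the stated 111. The sample size is sound on its own inputs and does not depend on the rule under review.

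**Formulas.** Let r1 and r0 be the shares observed (intervention, control), p1 and p0 the rates among those observed, and m1 and m0 the unknown rates among those missing.

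- Planned rule: r1·p1 - r0·p0
- Lower bound (m1 = 0, m0 = 1): r1·p1 - (r0·p0 + 1 - r0)
- True difference: r1·p1 + (1 - r1)·m1 - r0·p0 - (1 - r0)·m0

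The rule equals the lower bound only if no control outcome is missing.

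**Equal missingness, 30% per arm.**

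- Planned rule: 0.70 × 0.56 - 0.70 × 0.49 = 0.392 - 0.343 = +4.9 points (odds ratio 1.24).
- Lower bound: 0.392 - (0.343 + 0.30) = 0.392 - 0.643 = -25.1 points.
- Upper bound: 0.392 + 0.30 - 0.343 = +34.9 points.
- True difference in points: 4.9 + 30 × (m1 - m0). It is below 4.9 whenever m1 < m0, and reaches zero when m0 - m1 = 4.9/30 = 16.3 percentage points. With m1 = 20% and m0 = 40% it is 4.9 - 6.0 = -1.1 points.

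So the lower-bound claim fails without any imbalance in response.

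**Unequal missingness (assumed splits, each averaging 30%).** Entries are what the rule reports, in percentage points.

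| Missing, intervention v control | 49% in both arms | 56% v 49% |
|---|---|---|
| 30% v 30% | 0.0 | +4.9 |
| 27.5% v 32.5% | +2.5 | +7.5 |
| 25% v 35% | +4.9 | +10.2 |
| 35% v 25% | -4.9 | -0.4 |

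For example, 0.49 × 0.75 - 0.49 × 0.65 = 0.3675 - 0.3185 = 0.049, and 0.56 × 0.75 - 0.49 × 0.65 = 0.420 - 0.3185 = 0.1015. In the second case the supposed minimum exceeds the 7.0-point complete-case difference.

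Under no true effect, with 8 × 159 = 1,272 enrolled per arm (111/0.7 rounded up to 159) and a design effect at ICC 0.001, a two-sided normal test on the recoded data rejects in about 5% of trials at equal missingness. It rejects in about 23% at 27.5% v 32.5% and about 68% at 25% v 35%.

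**The case against.** The strongest reply is that little rests on this analysis. It is one of three robustness checks, read beside a weighted intention-to-treat analysis and a complete-case analysis. Descriptive statistics on loss to follow-up are planned, so a large imbalance should be visible. A minimum above the complete-case estimate would look odd at once. With equal missingness the rule simply shrinks the risk difference from 7.0 to 4.9 points, which is probably the conservative behaviour intended. All of this stands and limits the severity, but it does not make the result a minimum.

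A reader might infer that the rule will manufacture a benefit in this trial. The documents do not support that. They give no attrition by arm. Questionnaires go out by email with text-message reminders and no described difference between arms (Data collection), and survey participation is stated to be independent of the intensified intervention (Recruitment to the survey). The size and direction of any imbalance are unknown, and the reverse imbalance would hide an effect.

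The 30% is also uncertain here. The term *missing registrations* follows a clause about register records, and Table 3 lists the National Child Health Register as a second source for the outcome. If register outcomes are meant, the missing share is not given and the figures above do not carry over. The algebra does: any missing control outcome puts the rule above the lower bound.

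Finally, the opposite-extremes range is too wide to decide anything by itself. That is fair, and it is why that range should serve only as the limit of a graded analysis.

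**Conclusion.** The label is wrong as written. On the plan's rates, with 30% missing in each arm, the stated minimum of +4.9 points lies 30 points above the true lower bound of -25.1. A difference of about 16 percentage points between the missing mothers of the two arms is enough to remove the effect. This rests on reading the planned attrition as the missing share and on equal missingness. The results under unequal missingness rest on assumed splits and show only what the rule can do in either direction.

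Severity is moderate. A reader might infer that the trial's main conclusion is compromised, but it is not: the weighted estimate, the complete-case estimate and the sample size do not use this rule. Nor does the protocol say that it will report the effect as at least a given figure; it says that the scenario gauges the minimum. The error is in what that one analysis is said to show. An arm-specific analysis is proposed to replace a wrongly described method, not as detail that the article ought to have held.

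**What to change.** 1. Rename the scenario *missing = not exclusively breastfeeding in both arms*, and delete the worst-case and minimum-effect wording.
2. State whether missing registrations means survey outcomes, register outcomes, or both.
3. Report the number and share of missing four-month outcomes by arm next to the result.
4. Add an arm-specific tipping-point analysis: lower the assumed rate among missing intervention mothers relative to missing controls until the conclusion changes, and report the gap at which it does. Show the opposite-extremes bound only as the limit of that range.

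The cost is a change of wording and a few extra model runs, with no new data. The trade-off is that the reported floor becomes less favourable than the one that the present rule would give.

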### Multidisciplinary evaluation data

#### Difference-in-Difference design using register data

In the National Child Health Register, municipalities have been required to report data on exclusive breastfeeding since 2011. Difference-in-difference analyses will be applied to estimate the difference in change in proportions breastfeeding at four months, and in average number of weeks of breastfeeding from before (≤ 2021) to after (≥ 2022) the intervention period comparing the intervention and control arm. The advantage of this approach is that it will provide an estimate of the effect if treatment is upscaled to the entire country. The effect of the intensified intervention in the difference-in-difference analyses will be examined by including an interaction term like in the survey analyses. Data from national Danish registers will be retrieved on all mother–child dyads in the included 21 municipalities from 2015 to 2025. This part of the evaluation awaits data availability in the registries which is expected in early 2025 at the earliest. Table 3 provides information on the registers used.

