**Discussion:**

This study protocol reports on the design and evaluation of the Breastfeeding Trial – a cluster-randomised trial implemented within the Danish Municipal Health Visiting Programme from April 2022 to October 2023. The purpose of the programme is to streamline breastfeeding support provided across healthcare sectors. The evaluation approach is comprehensive using a multitude of data to analyse the effect of the intervention and inform future efforts to improve breastfeeding for all.

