**Development and implementation**
For the adaptation of the previous successful breastfeeding intervention done by Nilsson and colleagues (2017) in hospital setting, an assessment of the needs of families following discharge from hospital after birth and until six months postpartum was carried out. Programme objectives corresponding to findings from the needs assessment formed the basis of the adaptation. In the adaptation process, a participatory approach including health visitor representatives from each of the intervention municipalities was chosen to enhance ownership, to match the organisational structure of the setting (the Danish Health visiting programme), and to ensure implementation in the intervention municipalities. The final intervention programme consisted of a breastfeeding programme for parents and a related training programme for health visitors. In December 2021, 210 health visitors from the 11 intervention municipalities completed a preparatory 3.5-h e-learning course, and in March 2022 they participated in the 15-h physical attendance interactive training programme supported by a written manual. Following training, the health visitors immediately initiated implementation of the programme in their municipalities

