##### Intensified intervention

In the intervention arm, families in which the mothers are younger than 25 years when they give birth (young age) and/or have primary school or vocational training as their highest educational attainment (low education) are offered an intensified intervention following the same breastfeeding principles, but they will receive a higher dose of the intervention. The aim is for health visitors to be proactive in delivering support and preventing breastfeeding cessation in this group, which carries an increased risk of early cessation. The intensified intervention is delivered within the first five months through additional follow-up phone calls (*n* = 7) and a single extra visit, all of which are scheduled to occur in-between the home visits (see details in Additional File 1). If a mother receiving follow-up by telephone ceases breastfeeding, she will no longer receive the telephone follow-up. Families accepting the intensified intervention are free to decline further extra telephone calls and/or visits.

The intervention is expected to reach > 6,000 families in the trial period, of whom 30–40% are expected to be in the target group for the intensified intervention. After the trial period, health visitors in the control clusters will receive the training and supportive materials developed during the intervention.

Figure 2 presents the programme theory in a logic model structure. The programme theory guides evaluation by outlining our hypothesis as to which mechanisms drive intended changes in outputs and outcomes to be measured, e.g., the hypothesis that the breastfeeding support programme will promote frequent breastfeeding, which will increase the likelihood of establishing effective breastfeeding, among others because milk production is stimulated causing sufficient milk to reach the infant, which, in turn, is hypothesised to lower the risk of readmissions.

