### Data collection

The data collection period commenced on 26 April 2022, in both trial arms. From mid-June it has been possible to assess the full intervention in the intervention clusters, including monitoring the effect achieved by introducing breastfeeding counselling in the pregnancy visit. Local variations will exist in the duration of data collection due to a varying number of births in the clusters. Data collection is projected to end by October 2023 in the municipalities with fewest births.

The questionnaires are distributed to families via personal emails and followed up by two reminders sent by text message (SMS).

Mothers for whom reading and filling out a questionnaire are very challenging are offered a phone call or Microsoft Teams call by a project student assistant who will help them complete the questionnaire. At recruitment, the mother will decide whether to accept or decline this offer.

An overview of the data collection timeline is given in Fig. 3, and Table 3 shows which outcomes and covariates are collected from each survey wave.

**Table 3 Tab3:** Overview of quantitative data collection, source and timepoints

Outcome measures	Survey data						Register data
*Sources*	**Mother**					Partner	
Time point since birth (PP)	One week	One month	Four months	Six months	Twelve months	One month	

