### Patient and public involvement

The intervention was developed based on a previous successful study [27] and on a needs assessment [30] in a co-creation design with one to two health visitor representatives from each of the intervention clusters. The development was conducted in an iterative manner where health visitors tested aspects of the intervention in their real-world setting after having attended each meeting. The intervention was developed within a two-step approach: first, the contents and major outlines of the intervention were developed (January 2021 – April 2021). Next, co-creation with health visitor representatives from the intervention clusters was conducted following the described iterations (April 2021 – December 2021).

To be able to reduce social inequality in breastfeeding, it is important to investigate how the Breastfeeding Trial works in families who carry a high risk of early breastfeeding cessation, i.e., conceptualised in this study as families in which the mother is young or has a low educational attainment. These characteristics are in many ways stigmatised in high-income settings like Denmark [56, 57]. Therefore, it is essential that the intervention supports relationship built on trust and provides a sense of security between the health visitor and the family. In an effort to avoid this stigma, recruitment videos developed and employed as part of the intensified intervention were tested among mothers in the target group and revised according to their feedback. Additionally, parents in the risk group participated during the questionnaire development phase with testing of questionnaires, which generated valuable input for the process.

A reference group of parent organisations, practitioners and decision makers will be established in order to contribute knowledge and experience, qualifying the project and in the long term facilitating and ensuring the dissemination of the project and ensuring that the knowledge produced will be targeted the audience including relevant decision makers.

During monthly dialogue meetings, health visitors will have the opportunity to disclose information about any harms or adverse effects. As the intervention aims to strengthen existing standard care, it is not expected to induce harm to the study population, and no data monitoring committee has been established.

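### The register difference-in-difference analysis counts every birth from 2022 on as 'after', including births before the programme began and births after the control arm is trained, so its estimate is diluted if the programme works

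*Protocol article*

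**What the plan says.** The section on the difference-in-difference design estimates the change in the proportion breastfeeding at four months, and in average weeks of breastfeeding, between arms. The earlier period is ≤ 2021. The later one is written as (≥ "2022) the intervention period comparing the intervention and control arm". The same paragraph retrieves data on all "dyads in the included 21 municipalities from 2015 to 2025". It gives no last birth date, no transition period and no rule for control births once the control arm has been trained.

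Other sections give the timeline:

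- Table 2 (development and implementation): "in March 2022 they participated in the 15-h physical attendance interactive training programme", and "Following training, the health visitors immediately initiated implementation of the programme in their municipalities".
- Abstract, Discussion: the trial is "implemented within the Danish Municipal Health Visiting Programme from April 2022 to October 2023".
- Eligibility criteria: the project period for eligible births runs from April 2022 to the end of 2023.
- Intensified intervention: "After the trial period, health visitors in the control clusters will receive the training and supportive materials developed during the intervention". No date is given for this.
- Statistical methods: a survey sensitivity analysis separates 26 April-16 June 2022 from 17 June 2022 onward, because pregnancy visits were added in June.

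**The concern.** A difference-in-difference estimate has its intended meaning only while one arm is exposed and the other is not. The stated rule pools three kinds of birth under 'after':

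- births before the programme was delivered;
- births with a true contrast between arms;
- births after both arms have been trained.

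The first and third kinds carry little or no contrast and average the effect toward zero. The article separates exposure phases to the day for the survey but uses whole calendar years for the registers.

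The analysis is supplementary but not trivial. The abstract says that effectiveness will be judged on survey and register data, and Table 3 lists the National Child Health Register as a source for both primary outcomes. The article also claims that this design shows what would happen if the programme were upscaled nationally. A diluted estimate does not answer that question, and it could be misread as failing to support a survey effect.

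**Working it through.** **Planned effect.** The article gives no power figure for the register analysis, so the yardstick is the survey's design effect (Sample size and power calculations): 49% to 56%, that is 7 points. The odds ratio is (0.56/0.44)/(0.49/0.51) = 1.325, against 1.32 stated. The 111 mothers per cluster also reproduces. Two proportions at 80% power and two-sided 5% need 798 per arm. With eight clusters per arm and an ICC of 0.001, m = 798 × 0.999/(8 − 0.798) = 110.7. So 7 points is the effect the trial was built on.

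**Days in the 'after' period, taking births as even over time**

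- 2022-2025: 365 + 365 + 366 + 365 = 1,461 days. 2022-2024: 1,096 days.
- January-March 2022: 90 days, or 90/1,461 = 6.2%.
- Contrast period from 1 April 2022: 275 + 304 = 579 days to the end of October 2023, or 275 + 365 = 640 days to the end of December 2023.
- After the trial period, to the end of 2025: 61 + 731 = 792 days (54.2%) or 731 days (50.0%).

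**Effect remaining.** Let c be the fraction of the effect that trained controls gain. Then

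share = [contrast days + (1 − c) × later days] / total days, and average effect = 7 × share.

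| Data to | Control catch-up | End October 2023 | End December 2023 |
|---|---|---|---|
| 2025 | full (c = 1) | 579/1,461 = 39.6%, 2.8 points | 640/1,461 = 43.8%, 3.1 points |
| 2024 | full (c = 1) | 579/1,096 = 52.8%, 3.7 points | 640/1,096 = 58.4%, 4.1 points |
| 2025 | half (c = 0.5) | (579 + 396)/1,461 = 66.7%, 4.7 points | (640 + 365.5)/1,461 = 68.8%, 4.8 points |

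For comparison, a window closed at the end of 2023 would keep 579/730 = 79.3% to 640/730 = 87.7% (5.6-6.1 points) under full catch-up. The late tail is therefore the larger problem and the early months the smaller one.

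**Limits of this arithmetic.** January-March 2022 births are scored as unexposed. Many had later standard visits, at two and at four to six months, from trained staff, so the early loss is an upper bound. In the other direction, births in the last four months before control training are scored as fully contrasted, although their outcome falls after it. The programme effect is taken as constant over time. The article also does not say whether the year refers to birth or to outcome; birth is assumed here.

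**The case against.** **Supplementary status and condensation.** The section on outcome measures says the trial was designed around survey measures and calls the other sources supplementary. An article may leave exact windows to the full plan, and register data were not expected before early 2025. This limits the consequence, and it means that the correction was still possible when the article was written. It does not remove the defect: the article states a numeric cut-off, and that cut-off conflicts with its own dates.

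**Retrieval range.** 2015 to 2025 is what will be retrieved, not expressly what enters the contrast. That is fair, and it is why results to the end of 2024 are also shown. But as written nothing excludes 2024-2025 births from ≥ 2022.

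**Instant, full catch-up is a worst case.** This stands. Controls are promised training and materials; the text does not say that they also receive pregnancy visits or the intensified follow-up. The half catch-up row addresses this.

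**Stronger readings that the documents do not support**

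- A reader might date the programme from "The data collection period commenced on 26 April 2022, in both trial arms" and count all earlier 2022 births as unexposed. That is the start of survey data collection; delivery began directly after the March training.
- A reader might call the baseline contaminated because "health visitors tested aspects of the intervention in their real-world setting after having attended each meeting" during 2021. Those were one or two representatives from each of 11 municipalities: 11-22 of 210 health visitors (5-10%), for 9 of the 84 months in 2015-2021, or roughly 1% of baseline exposure at most. The December 2021 e-learning was preparatory. This does not justify dropping 2021, the pre-period year closest to the start.
- A reader might see this as the only guard against survey selection and dropout. The survey analysis is also linked to registers covering all births and weighted for missing outcomes.

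**Conclusion.** The point holds for the supplementary register analysis. The stated 'after' period mixes partly exposed, contrasted and crossed-over births, and the bias is toward no effect if the programme works. About 6% of a 2022-2025 window precedes April 2022, and 50-54% follows the trial period.

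The dilution is a range, not a single figure: about 40-44% of the effect remains with full control catch-up and data to 2025, 53-58% with data to 2024, and 67-69% with half catch-up and data to 2025. These figures rest on even births, a 1 April 2022 start, control training at the end of the trial period and a constant effect. The control training date and its uptake are unknown. The survey-based primary analysis and its sample size are unaffected.

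**What to change.** Before register outcomes are examined, define the periods by birth date, identically in both arms:

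- **Before:** births to the end of 2021. Exclude 2021 only as a sensitivity analysis.
- **Transition:** leave January-March 2022 births out of the main contrast.
- **After:** from programme start in April 2022 to the last birth whose four-month outcome falls before the first control municipality is trained.
- **Post-roll-out:** report later births separately and do not pool them into the effect estimate.

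Also record when each control municipality is trained, and give one end date for the trial period in place of October 2023 and end of 2023.

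The cost is wording, fewer 'after' births and so somewhat lower precision. If the first control training fell on 1 November 2023, the 'after' period would cover births from 1 April 2022 to about 30 June 2023 (275 + 181 = 456 days). If it fell on 1 January 2024, it would run to about 31 August 2023 (275 + 243 = 518 days). The births given up carry little of the contrast, or only part of it.
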